## Abstract

**Background:**

The uptake of Intermittent Preventive Treatment of malaria in pregnancy using Sulfadoxine-Pyrimethamine (IPTp-SP) remains unacceptably low, with more than two-thirds of pregnant women in sub-Saharan Africa still not accessing the three or more doses recommended by the World Health Organisation (WHO). In contrast, the coverage of Seasonal Malaria Chemoprevention (SMC), a more recent strategy recommended by the WHO for malaria prevention in children under five years living in Sahelian countries with seasonal transmission, including Mali and Burkina-Faso, is high (up to 90%). We hypothesized that IPTp-SP delivery to pregnant women through SMC alongside antenatal care (ANC) will increase IPTp-SP coverage, boost ANC attendance, and increase public health impact. This protocol describes the approach to assess acceptability, feasibility, effectiveness, and cost-effectiveness of the integrated strategy.

**Methods and analysis:**

This is a multicentre, cluster-randomized, implementation trial of IPTp-SP delivery through ANC + SMC vs ANC alone in 40 health facilities and their catchment populations (20 clusters per arm). The intervention will consist of monthly administration of IPTp-SP through four monthly rounds of SMC during the malaria transmission season (July to October), for two consecutive years. Effectiveness of the strategy to increase coverage of three or more doses of IPTp-SP (IPTp3 +) will be assessed using household surveys and ANC exit interviews. Statistical analysis of IPT3 + and four or more ANC uptake will use a generalized linear mixed model. Feasibility and acceptability will be assessed through in-depth interviews and focus group discussions with health workers, pregnant women, and women with a child < 12 months.

**Discussion:**

This multicentre cluster randomized implementation trial powered to detect a 45% and 22% increase in IPTp-SP3 + uptake in Mali and Burkina-Faso, respectively, will generate evidence on the feasibility, acceptability, effectiveness, and cost-effectiveness of IPTp-SP delivered through the ANC + SMC channel. The intervention is designed to facilitate scalability and translation into policy by leveraging existing resources, while strengthening local capacities in research, health, and community institutions. Findings will inform the local national malaria control policies.

**Trial registration:**

Retrospectively registered on August 11th, 2022; registration # PACTR202208844472053.

Protocol v4.0 dated September 04, 2023.

Trail sponsor: University of Sciences Techniques and Technologies of Bamako (USTTB), Mali.

## Background

Malaria infection during pregnancy is a major public health problem, and a notable cause of adverse birth outcomes, including foetal loss, stillbirth, low birth weight and preterm birth [1]. In 2021, 32% of the estimated 40 million pregnancies were exposed to malaria infection in Sub-Saharan Africa (SSA), which would have resulted in 961,000 low birth weight (LBW) children with no pregnancy-specific intervention [2]. To overcome the latter, the World Health Organization (WHO) recommends the use of intermittent preventive treatment with sulfadoxine-pyrimethamine to prevent malaria in pregnancy (IPTp-SP) in areas of moderate-to-high transmission in SSA [3]. However, IPTp-SP uptake remains unacceptably low [2]. Indeed, among the approximately 840 million people at risk of malaria in endemic countries in SSA, more than 30 million pregnant women could benefit from IPTp-SP each year. Still, during the last few years, WHO observed a decline in its coverage in several African countries. Indeed over two-thirds of pregnant women in SSA are still not accessing to the WHO-recommended three or more doses (IPTp3 +), and closing the gaps in access to proven malaria control tools is a top priority for the WHO Global Malaria Program [4].

Despite the implementation of this policy, in 2018 about 28% to 40% of pregnant women in Mali received IPTp3 + [5] when in Burkina Faso this figure was 58% [5]. In contrast, the coverage of Seasonal Malaria Chemoprevention (SMC) among children under 5 years in both countries and in other Sahelian countries of West Africa is high (up to 90%) [5]. SMC is a relatively new strategy recommended by the WHO in 2012 for malaria control in Sahelian countries with seasonal malaria transmission such as Mali and Burkina Faso. It consists of the administration of a single dose of SP plus three daily administrations of amodiaquine (SP + 3AQ) to children aged 3–59 months during the high malaria transmission season, involving four rounds of SP + 3AQ at monthly intervals. SMC is provided at fixed or door-to- door delivery (DDD) visits by community health workers (CHWs) or community relays (CRs). In the two countries, and in other Sahelian countries, both fixed and DDD strategies provide good coverage though DDD provides higher coverage [6].

Thus, we hypothesized that IPTp-SP delivery to pregnant women through the SMC channel using DDD approach will increase IPTp-SP coverage and achieve greater public health impact, as the risk of malaria and its burden on birth outcomes increases during the rainy season corresponding also to the period of SMC [7, 8]. Reported increases in two or more doses (IPTp2 +) and IPTp3 + coverage with community-based IPTp-SP administration vary considerably by country and baseline IPTp-SP coverage [9–14]. Recently, in Burkina Faso, IPTp-SP administration by CHWs (outside the SMC distribution channel) resulted in a relative increase of 17.6% in IPTp3 uptake [9]. In addition the IPTp-SP coverage has lagged behind antenatal care (ANC) coverage for years, and the integrated strategy has the potential to substantially boost it. Indeed, by giving SP in the community through CHWs and CRs during the high malaria transmission season when ANC access is reduced, whilst also mobilizing pregnant women to attend ANC, the strategy may also boost ANC attendance and uptake of the latest WHO ANC recommendations of eight ANC contacts during pregnancy [15].

The COVID-19 pandemic also posed important considerations for health care systems and service delivery in SSA. This study will explore strategies to address the likely decrease in the uptake of ANC services in the study population because of the COVID-19.

## Methods/Designs

### Objectives and hypothesis

The main objective of this study is to evaluate whether the integration of IPTp-SP delivery to SMC in addition to ANC delivery will increase the coverage of IPTp-SP and ANC among pregnant women in Mali and Burkina Faso. The primary hypothesis is that integrated ANC + SMC strategy (intervention) as compared to the ANC (standard of care) will increase coverage defined as an increase in coverage of ‘at least 3 doses’ of IPTp-SP, by 45% in Mali and 22% in Burkina Faso, and support the goal of improving the prevention of malaria in pregnancy and reducing adverse birth outcomes in Sahelian pregnant women.

The primary objectives are: (1) to compare the delivery of IPTp-SP through the integrated strategy with standard of care, (2) to assess the acceptability and feasibility among health providers and pregnant women, (3) to assess the systems effectiveness at implementing the integrated delivery strategy and (4) to estimate the incremental cost-effectiveness of the integrated versus standard of care strategy from the societal perspective. (Economic protocol to be published separately).

The secondary objectives are: (1) to assess any increase or decrease in SMC or ANC uptake following the integrated ANC + SMC IPTp-SP implementation, (2) to estimate the number of malaria cases in both children and pregnant women over the course of the trial, and (3) to assess pregnancy outcomes at delivery (birth weight, miscarriage, stillbirth, preterm birth) in both the intervention and control arms among women delivering at health facilities (HF).

An exploratory objective will assess women’s ANC and IPTp-SP care seeking practices and any impact that the COVID-19 pandemic had on their delivery and access.

### Study design

This is a multicenter, cluster randomized, implementation trial of IPTp-SP delivery in two parallel arms (ANC alone and ANC + SMC) at 40 HFs and their catchment communities (20 clusters per arm). The design and the data collection timelines are illustrated in Fig. 1.

**Fig. 1 Fig1:**
[figure not shown]
Study design and timeline

#### Study population

Pregnant women and women with a child under 12 months of age, healthcare providers, Community Health Workers (CHWs) and or Community Relays (CRs), District Health Management Team staff.

#### Inclusion criteria

Clusters: Government and community owned HFs.Participants living in the catchment area of selected government and community HFs in the study sites/clusters.Participants’ written informed consent.

#### Exclusion criteria

Private HFs, ANC attendees of private HFs and staff of private HFs.

#### Sampling methods

Four household surveys (HHS) will be carried out. Two at baseline, one to assess participants’ baseline characteristics, IPTp-SP coverage, and ANC attendance rate, and one for SMC coverage. Two at endline, one to measure the primary endpoint (i.e., IPTp3 + coverage) and one to measure SMC coverage. In each country, a multi-stage cluster sampling method will be followed to select the clusters (health facility and its catchment area) from the study sites that will be included in the HHS. The sampling will be carried out in three stages in each study site (Fig. 2), namely: (1) random selection of ‘clusters’ using probability proportional to size (PPS); (2) random selection of households in each ‘cluster’ using maps and household listing. Mapping and listing of the households will be completed before the baseline IPTp-SP or SMC HHS begins. These households will be selected by equal probability; (3) simple random selection of the woman or guardians of SMC children to be interviewed in each household among those meeting the inclusion criteria. A single child will be selected per HH to minimize the cluster effect. When several eligible women are present in a household, the woman with the most recent birth will be chosen.

**Fig. 2 Fig2:**
[figure not shown]
Sampling methods

The same sampling methods will be used for the baseline and endline HHS, except for stage 1 (i.e., selection of ‘clusters’ by PPS) which at endline will be stratified by arm.

### Study site

The study is conducted in two Sahelian countries with highly seasonal malaria transmission where SMC has been implemented since 2012 (Fig. 3). In Burkina Faso, the study site is Boussé District located at 55 kms North-East from Ouagadougou. The population in 2019 was estimated at 189,937 inhabitants [16]. In 2020, the coverage of IPTp3 + and SMC was 55.9% and 103%, respectively [17]. In Mali, the study site is the district of Kangaba located at 85 kms South-West of Bamako with an estimated population of 146,563 inhabitants in 2021. The district belongs to the region of Koulikoro which has 33.8% coverage of IPTp3 + [18] and that of SMC at > 100% in the district [19].

**Fig. 3 Fig3:**
[figure not shown]
Study sites

### Randomization and treatment allocation

Randomization will be done prior to the baseline survey but kept concealed until the completion of the baseline survey. Clusters will be randomly allocated at a ratio of 1:1 to the intervention and control arms. The unit of randomization will be HF and its catchment area to avoid contamination between ANC providers in the same service. Therefore, each HF and its respective community will form a cluster. Each HF will be randomly assigned to either:

1) the delivery of IPTp-SP to pregnant women during SMC implementation + ANC (intervention); or 2) delivery of IPTp-SP using standard ANC delivery (control).

SP will be provided by the study in both intervention and control sites to avoid stock-outs. To minimize any risk of allocation bias, all participating HFs will be randomized simultaneously.Intervention arm

The intervention will consist of the monthly provision of IPTp-SP through the SMC channel during the four monthly rounds (July to October) for two consecutive years (Fig. 4).

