### Sample size calculation

#### Primary endpoint – IPTp3 + at endline

The primary endpoint will be collected at endline among women with a child less than 12 months.. It will be the individual level binary indicator for presence or absence of at least three doses of IPTp-SP through ANC alone or ANC plus SMC delivery platforms. Since baseline prevalence of IPTp-SP coverage highly differs between Mali and Burkina Faso, the sample size was calculated for each country separately.

In Mali, with 10 clusters per arm, 48 women sampled per cluster will be required at endline to detect a 45% increase in the relative risk of women receiving at least 3 doses of IPTp-SP between control and intervention arms, with 80% power, alpha = 5%, an intra-cluster correlation coefficient (ICC) of 2.5% and 5% primary endpoint missing rate, assuming this proportion to be 28% in the control arm [20]. Based on this assumption a total of 1,008 women will be included (Shiny CRT calculator®) [21]. With this sample size, we should be able to demonstrate a 33% in the relative risk of women receiving at least 3 doses of IPTp-SP assuming this proportion to be 40% in the control arm as recently reported in an HHS conducted in a neighboring area, Bankass in Mopti region ([name] et al., 2022, unpublished data). Assuming that there will be at least one eligible woman in every 5 households, a total of 5,040 households will be visited.

In Burkina Faso, with 10 clusters per arm, 46 women sampled per cluster will be required at endline to detect an increase of 22% in the relative risk of women with at least 3 doses of IPTp-SP between the control and intervention arms, with 80% power, alpha = 5%, an ICC of 2.5% and 5% primary endpoint missing rate, assuming this proportion to be 58% in the control arm [18]. Based on this assumption a total of 966 women will be included. Assuming that there will be at least one eligible woman in every 5 households, a total of 4,830 households will be visited.

A possible adjustment of the number of women to be interviewed in the endline surveys will be made based on the baseline data: IPT3 + coverage; proportion of non-response and calculated ICC.

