#### Secondary endpoints

Feasibility and acceptability

To assess the acceptability and feasibility of IPTp-SP delivery through the ANC + SMC strategy, a purposive sample of 40 to 80 pregnant women of different gravidities and women with a child < 12 months. per country (80 to 160 total) will be recruited at endline. An additional purposive sample of 48 to 72 women will be selected for Focus Group Discussions (FGDs). Two to four health providers purposively selected from each of the 10 intervention HFs in each country (40 to 80 total) and all consenting CHWs who were involved in the IPTp-SP community delivery will be included. The interviews will also include the DHMTs and Ministry of Health staff in the National Malaria Control and Reproductive Health departments (approx. 5 per site, *n* = 10).Systems effectiveness

ANC exit interviews will be conducted with pregnant women when leaving the HF at endline to assess the systems effectiveness of the IPTp-SP delivery in both arms (intervention and control). In Mali, a sample size of 699 women from 20 HF will allow the detection of an estimated 35% of women achieving the primary endpoint of IPTp3 + with a precision of ± 5%, 95% CI, and a DE of 2. In Burkina Faso, a sample size of 699 women from 20 HF will allow the detection of an estimated 65% of women achieving the primary endpoint of IPTp3 + with a precision of ± 5%, 95% CI, and a DE of 2.Exploratory COVID

To assess women’s ANC and IPTp-SP care seeking practices and any impact that the COVID-19 pandemic had on delivery and access at baseline, a purposive sample of 8–12 pregnant women of different gravidities and women with a child < 12 months. will be selected (80–120 women per country for a total of 160–240) for FGD, and a purposive sample of 2–3 health care providers will be selected from 10 HFs in both countries (20–30 per country for a total of 40–60) for in-depth interviews.

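### Drawing the allocation before the baseline survey gains nothing for concealment and gives up balancing 10 clusters per arm on baseline IPTp3+ coverage

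*Protocol article*

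**What the plan says.** Under *Randomization and treatment allocation*, the protocol article fixes the order of events: "Randomization will be done prior to the baseline survey but kept concealed until the completion of the baseline survey". On the draw itself it says "Clusters will be randomly allocated at a ratio of 1:1 to the intervention and control arms" and "all participating HFs will be randomized simultaneously".

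Under *Sampling methods*, the baseline household survey is there to measure IPTp-SP coverage and ANC attendance, among other characteristics. Clusters enter that survey by PPS selection.

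The *Sample size calculation* treats the countries separately: "In Mali, with 10 clusters per arm, 48 women sampled per cluster will be required at endline", and "In Burkina Faso, with 10 clusters per arm, 46 women sampled per cluster will be required at endline". It uses an ICC of 2.5%, and it lets baseline coverage, non-response and ICC revise the number of women at endline. The *Analysis plan* makes the by-country comparison primary, among women in the endline survey, using a logistic mixed model with a random intercept for cluster-period.

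**The concern.** Nobody is to know the arms until the baseline survey has finished. A draw made after the survey meets that aim equally well, because during the survey there is no list to leak. The early draw therefore brings no stated benefit. It has a cost: the restriction of the draw, if any, cannot use the coverage measured in the baseline survey, which is the most direct available predictor of the primary outcome.

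With only 10 clusters per arm in each primary comparison, chance can separate the arms before the intervention starts by an amount that matters beside the effect sought. If one arm in one country starts 5 points ahead, readers will struggle with a by-country estimate even though the test is valid. The plan already intends to use baseline coverage and ICC to resize the endline survey, but the chosen order makes the same data unavailable for balancing the arms.

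**Working it through.** **Inputs** (*Sample size calculation*, *Table 1*): 10 clusters per arm per country; ICC 0.025; Mali control 28%, relative increase 45%, 48 women per cluster; Burkina Faso control 58%, relative increase 22%, 46 per cluster; baseline samples 775 and 786. A two-sided 5% test is assumed.

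**1. The plan's own figures.** Targets are 0.28 × 0.45 = 12.6 points and 0.58 × 0.22 = 12.8 points. The unpooled two-proportion formula gives n = 219 (Mali) and 218 (Burkina Faso) per arm before clustering. Solving for women per cluster, m = n(1 − ICC)/(10 − n × ICC):
- Mali: 219 × 0.975/(10 − 5.475) = 47.2; the plan has 48, and 20 × 48 × 1.05 = 1,008.
- Burkina Faso: 218 × 0.975/(10 − 5.45) = 46.7; the plan has 46, and 20 × 46 × 1.05 = 966.

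Both reproduce, with power 80.3% and 79.9%.

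**2. Chance imbalance implied by the stated ICC.** Between-cluster SD = √(ICC × p(1 − p)). SD of the difference in arm means = that × √(2/10).

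| | p | Between-cluster SD | SD of arm difference | 95% range | P(above 5 points) | Target |
|---|---|---|---|---|---|---|
| Mali | 28% | 7.1 | 3.2 | ±6.2 | 12% | 12.6 |
| Burkina Faso | 58% | 7.8 | 3.5 | ±6.8 | 15% | 12.8 |

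All but the probabilities are in percentage points. At the plan's alternative Mali control rate of 40%, the SD of the arm difference is 3.5 points and the probability 15%. Five points is about 40% of either target (5/12.6, 5/12.8).

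**3. How much baseline coverage could remove.** Assume that all 20 clusters per country are surveyed at baseline with equal numbers: 775/20 ≈ 39 women per cluster in Mali. The reliability of observed cluster coverage is 0.025/(0.025 + 0.975/39) = 0.50. Without the 5% non-response allowance (738/20 ≈ 37) it is 0.49. Burkina Faso (786/20 ≈ 39) gives the same.

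The removable share of the imbalance variance is reliability × r², where r is the correlation between a cluster's true coverage at baseline and its underlying coverage at endline. The documents give no value for r, so a range is shown.

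For Mali, the planned SE of the difference is √[(0.28 × 0.72 + 0.406 × 0.594) × 2.175/480] = 4.48 points, with design effect 1 + 47 × 0.025 = 2.175. The between-cluster part is 0.025/(0.025 + 0.975/48) = 55% of that variance. The adjusted SE is therefore 4.48 × √(1 − 0.55 × removable share).

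| r (assumed) | Removable share | SE, Mali (points) |
|---|---|---|
| 0.5 | 0.125 | 4.32 |
| 0.7 | 0.245 | 4.17 |
| 0.9 | 0.405 | 3.95 |
| 1.0 | 0.50 | 3.81 |

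Half is thus a ceiling.

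**The case against.** The case for leaving the plan alone has real force. Randomising before baseline with concealment is valid. The imbalance SDs come from the same 2.5% ICC that went into the sample size, so the stated power and the confidence intervals already carry them. Imbalance of this kind is ordinary random variation, not a defect. All of that stands, and it limits the point to precision and credibility.

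It is also fair that nothing in *Sampling methods* says every randomised cluster is in the baseline survey, so the gain in step 3 is conditional. Routine facility data or household listings that exist before the survey could support some restriction: balancing on cluster size, for example, does not need a later draw. Only the survey's own measurements are ruled out by the timing.

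The cluster-period random intercept might suggest that baseline data enter the model. However, the primary outcome is defined on women in the endline survey. If that intercept is the only random term, it also leaves a cluster's two periods unlinked. The statistical analysis plan may add a baseline covariate, and its absence from the article is not counted as an omission.

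Finally, registration was retrospective in August 2022 and this is version 4.0 of September 2023, so the draw has probably been made. That affects which remedy applies, but the analysis remedy remains open.

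**Conclusion.** The point holds as an improvement worth making. The stated order gives no concealment advantage and rules out restricting the draw on baseline IPTp3+ coverage and ANC attendance. The exposed chance imbalance has an SD of 3.2 points (Mali) and 3.5 points (Burkina Faso), with a 12% and 15% probability of exceeding 5 points. This rests on the plan's own ICC and control rates. At most about half of its variance is recoverable if all clusters are surveyed, and about a quarter at r = 0.7.

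Two stronger readings are tempting and are not supported.
- A reader might infer from a single 1:1 ratio applied simultaneously that 10 clusters per arm in each country is not secured. The sample size section fixes 10 per arm in each country, and *Secondary endpoints* refers to "Two to four health providers purposively selected from each of the 10 intervention HFs in each country". Simultaneous describes timing, not one pooled list, and the mechanism of stratification is detail that a condensed article leaves out.
- A reader might infer that imbalance biases the test or leaves the trial underpowered. It does neither.

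Nor can the argument be extended to malaria cases or birth outcomes. Balancing on household-survey IPTp3+ coverage does not target them.

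**What to change.** If the draw has not been made: make it after the baseline survey closes and before the first July round, within each country at 10:10, for all facilities at once as now planned. Use covariate-constrained or stratified randomisation on cluster-level baseline IPTp3+ coverage, with someone independent of delivery and survey teams holding the list. Include that coverage as a cluster-level covariate in the by-country model; without it, the interval does not reflect the balance achieved.

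If the draw has been made: keep it. Specify the same covariate in the by-country primary model before endline data are examined by arm, and report the allocation method used and the baseline balance by country.

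Either way, state whether all 20 clusters per country are in the baseline survey. If some are not, name a pre-intervention source for their coverage, such as ANC register data.

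The cost is one reordered step, a short script and one model term per country. The practical constraint is that a later draw must fit between baseline close-out and intervention training.
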